**Domain: Train and educate stakeholders**	
**Develop educational materials**	Educational materials will be developed including guidelines for identifying depression using PHQ-2 and PHQ-9 for screening; an information leaflet for the patients about depression and a list of nearby facilities for depression care; BA therapy manual and patient guide; a desktop guide for the physicians on depression management and antidepressant prescription
**Distribute educational materials**	Clinics will be provided with the following educational materials: guidelines for identifying depression using tools like PHQ-9, a list of nearby referral facilities to help service users access appropriate care, BA materials (facilitator and patient guide), a desktop guide for depression management including prescribing antidepressants, and a risk assessment protocol for suicide
**Conduct ongoing training**	The research team, with input from the implementation team, will develop or modify training packages on (i) identification of depression, for physicians and lay counsellors, (ii) BA training for counsellors and supervisors, and additional training for BA supervisors, (iii) depression management including prescription of antidepressants for the physicians, (vi) data management including maintaining the confidentiality of medical/clinical records and (v) the CC model including aspects of care coordination and the use of population registry utilising a bespoke spreadsheet or paper-based registers
**Make training dynamic**	The training will make use of interactive methods such as role-plays, discussions and experience sharing
**Use train-the-trainer strategies**	Our training method will use a train-the-trainer model for specific training where possible. Psychologists are already based at the head office/central location in SINA. The research team, experienced in identifying depression, delivering and supervising BA, will train the psychologists in (i) identifying depression, (ii) delivering BA, (iii) supervising BA, and (iv) training others in BA. The psychologists will further take on the role of BA trainers and actively lead the training for counsellors on BA and mental health specialists (psychiatrists) on BA supervision, during the rollout of CC. However, to support those newly trained trainers/supervisors, experienced BA trainers and supervisors who are a part of the research team will stay in touch remotely. PCPs will be trained by the psychiatrists on depression management including prescription of antidepressants
**Domain: Provide interactive assistance**	
**Facilitation**	The implementation will follow a guide developed for this purpose, following five stages of implementation: (i) exploration, (ii) preparing for practice change, (iii) training, (iv) launching care, and (v) sustainability. To develop a shared understanding of the guide, implementation, and research team members will meet and set agendas and plans before each implementation stage
**Provide local technical assistance**	Technical assistance will be taken for several matters relating to implementation from the SINA head office including but not limited to (i) identifying and hiring staff and developing/revising job descriptions, (ii) arranging and scheduling training, (iii) calling meetings to introduce change in practice, (iv) development and implementation of registry and tracking tools, (iv) any changes to consumer fees or other financial decisions, and (iv) scheduling case review and supervision meetings
**Provide clinical supervision**	Mental health specialists will include psychiatrists to provide consultation and supervision to counsellors and physicians on case reviews and caseload management, and BA supervision. A preliminary supervision format was developed from the co-design workshops and implementation team meetings. BA supervision and case review meetings are to be conducted remotely or in-person in a group format, including the counsellor, physician (if needed), and the psychiatrists, who can join via phone, Zoom, or other encrypted services. Additionally there will be drop-in sessions available and a Whatsgroup established, separate for counsellors, and physicians to facilitate contact with the psychiatrists if needed, at indicated specific times
**Domain: Support clinicians**	
**Remind clinicians**	Workflows and flowcharts will be developed with laminated copies pasted over the physician’s desks to act as a reminder as well as a quick reference guide
**Revise professional roles**	SINA head office will hire new staff or revise the roles of the existing staff for clinics that are randomised to intervention group. Lay counsellors (where not already available), and psychiatrists will be hired. However, the roles of physicians and psychologists currently employed by SINA will be revised. Lay counsellors will work full-time, 6 days a week, supporting and coordinating mental health care, delivering BA, monitoring treatment response, and scheduling weekly care reviews and supervision meetings. Two part-time psychiatrists (approximately 3 h per week) will provide consultations to 6 clinics each, advising on medications and treatment strategies, and participating in weekly case review meetings. The physicians in all the clinics will take on additional duties, including identification of depression, prescribing antidepressants as needed, updating depression scores and clinical observations in clinic records, referring patients to counsellors, adjusting antidepressant doses through systematic tracking, and attending case review meetings when required. Two psychologists from SINA will serve as BA master trainers, ensuring delivery of BA training to new lay counsellors recruited for the intervention sites. Job descriptions for all those with revised roles or hired will be updated
**Facilitate relay of clinical data to providers**	The physicians will collaborate with lay counsellors via shared access to patient records and participate in weekly case reviews
**Domain: Change infrastructure**	
**Change physical structure and equipment**	The physical infrastructure and resources needed to implement CC will be identified and arranged, including dedicated rooms for counsellors, necessary furniture, tools for tracking and monitoring routine data, supply of antidepressants
**Change record systems**	A paper-based record system through a screening record register will be implemented to keep a record of the number of patients screened and also to monitor the screening interval for individual patients. In addition, the EMR interface (where it is available) will also be edited if possible, to allow entry of patient screening records

^*^Based on Expert Recommendations for Implementing Change (ERIC) implementation strategies

Figure 3 presents a visual presentation of our implementation strategies and how they are linked to different components of healthcare systems.

**Fig. 3 Fig3:**
[figure not shown]
Illustration of implementation strategies

### Optimised usual care

Clinics assigned to the OUC will follow the usual care pathway with some adjustments. The existing SINA care pathway for mental health varies depending on availability of the lay counsellor. If a counsellor is present, PCPs refer patients with distress symptoms for further evaluation, using tools like PHQ-4, PHQ-9, GAD-7 [42], and suicide risk assessment. If depression or anxiety is detected, counselling therapy is provided. In clinics without a counsellor, there is no formal system for identification of mental illness. As part of the OUC, we will introduce following changes: (i) all physicians will administer the PHQ-2 screening for depression to all patients aged ≥ 18, and if the PHQ-2 score is ≥ 3, physicians will refer patients to the counsellor and provide a leaflet with information about depression symptoms, treatment options, and nearby free mental health services and (ii) counsellors will be hired for clinics where there is not one available currently, who will screen patients using PHQ-9 and provide the usual care counselling therapy for those scoring ≥ 10.

### Outcomes

Outcomes in this trial are guided by the Reach, Effectiveness, Adoption, Implementation and Maintenance (RE-AIM) framework [48]. We will assess individual-level outcomes (for consenting trial participants) and clinic-level outcomes from aggregated, anonymised, routinely collected data in clinics (Table 3). For individual-level data, participant recruitment date will be used as a reference point for follow-ups, whereas reference point for clinical outcomes will be the CC rollout in the clinics. Table 3 shows the planned schedule of enrolment, interventions, and assessments.

**Table 3 Tab3:** Enrolment, interventions, and assessments schedule

	**Study period**				
	**Enrolment**	**Baseline**	**Post-allocation**		**Close-out**
**Timepoints**	** − 7 days**	**0 days**	**3 months**	**6 months**	**12 months**
**ENROLMENT**					
PHQ-2 screening by physicians	X				
Eligibility screening by researcher (PHQ-9; age and current treatment)	X				
Informed consent	X				
Allocation	X				
**INTERVENTIONS**					
Collaborative Care	■				
Optimised Usual Care	■				
**ASSESSMENTS**					
**Individual level data—those consenting to trial (starting/baseline point – date of participant recruitment)**					
Demographics		X			
Education, employment status and language		X			
Socioeconomic status (SES)		X			
Blood tests (haemoglobin, glycosylated haemoglobin (HBA1c)		X			
BMI, BP and waist circumference		X	X	X	X
**Effectiveness**					
Depression severity (PHQ-9)				X	
Depression caseness (PHQ-9)		X	X	X	X
Anxiety severity and caseness (GAD-7)		X	X	X	X
Quality of life (EQ-5D-5L)		X	X	X	X
Functional Impairment (WHODAS 2.0)		X		X	X
Healthcare resource (Modified CSRI)		X		X	X
Economic outcomes		X		X	X
Adverse events			X	X	X
**Clinics level data—aggregated data (starting point/baseline – after setting up CC in clinics)**					
**Reach**					
Receipt of treatment for depression				X	
Depression screening		X	X	X	X
**Adoption**					
Referral rate			X	X	
Supervisions			X	X	
**Implementation**					
BA completion rate		X	X	X	X
BA dropout rate		X	X	X	X
Antidepressants dispense rate			X	X	X
Antidepressants			X	X	X
**Maintenance**					
Sustainability			X	X	X
Equity			X	X	X

#### Primary outcome—effectiveness

The primary outcome is the depression severity measured at 6 months by estimating the mean change in PHQ-9 depression scores from baseline to 6 months and comparing across allocation groups [37, 38].

#### Secondary outcomes—effectiveness

The prevalence of case-level depression by allocation groups will be measured using PHQ-9 scores; a score < 10 indicates recovery, while ≥ 10 indicates case-level depression [37, 49, 50].The severity of anxiety will be measured by the mean change in GAD-7 scores from baseline to follow-up time points, across allocation groups. We will also assess the caseness of anxiety by allocation groups, using a GAD-7 score of ≥ 6 to indicate the clinical case-level of anxiety [38, 42].The mean change in Health Related Quality of Life (HRQoL) from baseline to follow-up time points, by allocation groups, will be measured using the EuroQol Five-Dimensional Scale, five levels (EQ-5D-5L) instrument [43].The severity of functional impairment will be measured by the mean change from baseline to follow-up time points by allocation groups using the World Health Organization Disability Assessment Schedule (WHODAS 2.0) [44].Anthropometric measures include BMI, BP, and waist circumference [51].Healthcare resource use will be assessed using a modified Client Service Receipt Inventory (CSRI). We will collect data covering several aspects including (i) outpatient and inpatient visits/admissions, (ii) medical tests, (iii) medicines, and (iv) details of specialities consulted. Costs will include total healthcare and out-of-pocket costs, including intervention costs [45].Economic outcomes such as household expenditures and assets, productivity loss, and catastrophic healthcare costs will also be collected. This will be collected using the International Wealth Index (IWI) and some items will be developed purposefully to capture this detail [41].Serious adverse events will be recorded and reported immediately, while adverse events will be recorded in follow-up.

Depression, anxiety, quality of life, anthropometric measures, and adverse events will be assessed at 3, 6, and 12 months. All other outcomes will be assessed at 6- and 12-month follow-up.

#### Primary outcome—implementation

Our primary outcome is the reach of depression treatment, measured by calculating the proportion of eligible individuals (score on PHQ-9 ≥ 10) who participate in treatment for depression (having ≥ two contacts with healthcare staff) 6 months after the CC rollout in the clinics, i.e. when clinic staff start practising CC in their clinics, referred to as the ‘start date’.

#### Secondary outcomes—implementation

Secondary implementation outcomes include:The reach of screening as the percentage of people attending clinics who participated in screening for depression (PHQ-2 and PHQ-9) at least once.Adoption of the intervention will be determined at 3 and 6 months through referral rates (number of patients referred for treatment divided by number of eligible patients). We will consider referrals, including within primary care settings and to specialised facilities if required. We will track the number of healthcare staff invited to training, those who attend, and the average number of supervision or case review meetings attended by staff each month. These metrics will be assessed in the 3rd and 6th month follow-up after the start date.The implementation of the CC components will be assessed using treatment engagement and dropout rates. We will determine the enrollment, completion, and dropout rates for psychotherapy (BA therapy in intervention clinics and any psychotherapy delivered in control clinics). Individuals who attend ≥ 2 sessions will be categorised as ‘engaged with BA/any psychotherapy’, whereas those attending < 2 sessions will be considered dropouts. We will also evaluate the prescription and adherence rates of antidepressants using the total number of antidepressants prescribed and the participants who complete their prescribed course of antidepressant medication captured through patient self-reporting.Sustainability will be assessed by comparing reach, BA completion and dropout, antidepressant prescription, and compliance rate over time.Equity in the treatment is the just distribution of treatment services, ensuring the participation of all individuals regardless of their socioeconomic status (SES) and demographic backgrounds. To ascertain equity, we will compare implementation outcomes mentioned above by SES and demographics (age, sex, ethnicity, education level).

Unless otherwise stated above, all outcomes will be recorded and compared across allocation groups, where feasible at all time points (3, 6, and 12 months after the start date).

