Key secondary outcome(s)	The following secondary outcomes related to clinical effectiveness will be measured at the participant level during follow-ups at 3, 6, and 12 months, unless otherwise specified below: 1. Body mass index (BMI) calculated using the formula: BMI = weight (kg)/height (m^2^), where height is measured in metres and weight is measured in kilograms 2. Blood pressure measured using an automated blood pressure instrument 3. Waist circumference measured in centimetres 4. Depression severity measured using PHQ-9 at 3 and 12 months 5. Depression caseness measured using PHQ-9 6. Anxiety caseness and severity measured using Generalised Anxiety Disorder Questionnaire (GAD-7) 7. Quality of life measured using Euroqol’s instrument EQ-5D-5L 8. Functional impairment measured using the WHO Disability Assessment Schedule (WHODAS 2.0) at 6 and 12 months 9. Healthcare resource measured using modified Client Service Receipt Inventory (CSRI) at 6 and 12 months 10. Adverse events measured using a modified adverse event The following clinic-level aggregated secondary outcomes related to implementation effectiveness will be calculated at 3, 6, and 12 months follow-up timepoints, unless otherwise specified below: 11. Reach of screening (RS) calculated using the formula RS = sd/nc, where ‘sd’ represents the number of individuals screened for depression and ‘nc’ denotes the total number of individuals attending the clinics 12. Reach of depression treatment (RT) calculated using RT = st/ne, where ‘st’ represents the number of individuals who participated in the treatment for depression and ‘ne’ represents the number of people eligible for such treatment at 3 and 12 months 13. Adoption (AD) calculated using AD = r/nr, where ‘r’ denotes the number of people referred for the treatment of depression and ‘nr’ denotes the number of people eligible for referrals at 3, and 6 months 14. Treatment enrolment (TE) calculated using TE = te/ne, where ‘te’ represents the number of people enrolled in the treatment of depression and ‘ne’ represents the number of people eligible for such treatment 15. Treatment completion (TC) calculated using TC = tc/te, where ‘tc’ represents the number of people completed the depression treatment and ‘te’ the number of people enrolled in such treatment 16. Treatment drop (TD) calculated using TD = td/te, where ‘td’ represents the number of people dropped out of the depression treatment and ‘te’ the number of people enrolled in such treatment 17. Sustainability calculated using change in percentage from baseline to follow-up time-points in reach, adoption, treatment enrolment, completion, and dropout 18. Equity by comparing reach, adoption, treatment enrolment, completion, and dropout across different levels of socioeconomic status, gender, and ethnicity

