### Recruitment

Recruitment of patients will be based on a two-stage screening process. All patients attending the trial clinics will be screened by trained PCPs for depressive symptoms initially using the PHQ-2 (a brief version of PHQ-9). Patients screening positive on PHQ-2 (score ≥ 3) will be referred to the counsellors for assessment using the PHQ-9. This will be implemented as part of routine practice in both the intervention and control clinics. To balance the intervention and control clinics except for the intervention, we plan to recruit counsellors for those trial clinics which do not have counsellors present currently.

In the intervention clinics as part of the CC model, patients who screen positive on PHQ-9 (score 10 or above) will be offered BA therapy, antidepressants, or their combination as per treatment protocol. In control clinics, optimised usual care (OUC) will be offered, including information leaflets and routine psychological treatment. Patients who fulfil the trial inclusion criteria will be approached by the researcher present, who will provide the study information sheet in the local language. Written informed consent will be obtained before trial enrolment. Where there are issues of literacy, the information will be read out by researchers and understanding checked; consent will be recorded via thumbprint signatures. Potential participants will be informed that their decision to take part in the study will not affect their entitlement to usual services and that they are free to withdraw from the study at any stage without having to provide a reason. If participants are willing to provide reasons for withdrawal, this will be recorded in the change of status form. There are no cross-overs intended as part of the trial design, and cross-overs of the trial participants between the intervention and control clinics are less likely to happen because of the separate catchment areas that the different clinics serve. However, the central electronic records system will help identify any potential cross-overs, in the unlikely case of it happening.

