#### Collaborative care model

The CC components co-designed considering the SINA context include the following: (i) two-stepped systematic identification of depression for all people aged ≥ 18. In the first stage, PCPs will screen patients using the PHQ-2, those scoring ≥ 3 will be referred to the lay counsellor. In the second stage, the counsellors will use the PHQ-9 to identify depression; (ii) counsellors will offer BA [38] therapy to patients scoring ≥ 10 on the PHQ-9. If a patient does not respond or prefers antidepressants, counsellors will refer the patient to the PCP to initiate antidepressant treatment; (iii) counsellors will track and monitor depression (e.g. the severity of depression symptoms) and process measures (e.g. number of contacts, care provided, and review with the mental health specialist) for all patients currently receiving care; (iv) counsellors and PCPs will collaboratively adjust care, using a stepped care approach such as augmenting BA with medication or changing the medication dose until care goals (improvement or remission of depression) are achieved; and (v) counsellors and PCPs (if required) will attend weekly supervision and case review meetings with the mental health specialists (See Fig. 2).

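### Treatment enrolment, completion and dropout cover all depression treatment in Table 1 but only psychotherapy in the outcomes text, which could disadvantage collaborative care where patients use antidepressants

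*Protocol article*

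**What the plan says.** The protocol article describes these outcomes in three places.

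- **Table 1, key secondary outcomes 14 to 16.** Enrolment is TE = te/ne, where te "represents the number of people enrolled in the treatment of depression" and ne is the number eligible. Completion is TC = tc/te, where tc "represents the number of people completed the depression treatment". Dropout is TD = td/te, where td "represents the number of people dropped out of the depression treatment". None of these is limited to one type of treatment.
- **Secondary outcomes—implementation.** "We will determine the enrollment, completion, and dropout rates for psychotherapy (BA therapy in intervention clinics and any psychotherapy delivered in control clinics" is the stated plan. Two or more sessions count as engaged, "whereas those attending < 2 sessions will be considered dropouts". Antidepressant prescription and adherence are measured separately.
- **Table 3, Implementation rows.** The labels are BA completion and "BA dropout rate", with separate antidepressant rows.

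The treatment pathway differs by arm. Under Recruitment, eligible patients in intervention clinics "will be offered BA therapy, antidepressants, or their combination as per treatment protocol". Under Collaborative care model, "If a patient does not respond or prefers antidepressants, counsellors will refer the patient to the PCP to initiate antidepressant treatment". Control patients are described, under Recruitment and Optimised usual care, as receiving a leaflet and counselling. Under Study setting, a few clinics are said to offer antidepressants already.

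Under Statistical methods, clinic-level outcomes other than reach are compared between arms with the same model as reach, where a comparison applies.

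**The concern.** One set of outcomes has an any-treatment population, a psychotherapy population and a BA population. This is not a detail left for the analysis plan. The article fixes the definitions, and they disagree.

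The disagreement decides how some patients are scored, and those patients are expected mainly in one arm. Intervention patients may receive antidepressants in place of BA or after it, as the pathway provides. A psychotherapy-only rule can read that as failure to enrol or to stay in treatment. Dropout and engagement are the stated measures of whether the components of collaborative care were implemented. Enrolment, completion and dropout also feed the sustainability and equity outcomes: Table 1 carries forward the any-treatment rates, while the outcomes text carries forward BA completion and dropout for sustainability.

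There is also a mismatch with the primary implementation outcome. Reach counts at least two contacts with healthcare staff and does not limit the type of treatment. A patient with two physician contacts for antidepressants can count as reached, yet appear as not enrolled or as a dropout in the secondary outcomes.

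**Working it through.** The plan gives no figure for these rates, so there is none to reproduce. The check sets the definitions side by side and then sketches the size under stated assumptions.

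**Scoring of four kinds of intervention patient**

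| Patient | Table 1 (any treatment) | Outcomes text (psychotherapy) |
|---|---|---|
| BA for two or more sessions, then antidepressants | Enrolled, still in treatment | Engaged |
| One BA session, then antidepressants | Enrolled, still in treatment | Dropout |
| Antidepressants from the start, no BA | Enrolled, still in treatment | Outside the dropout rate if the denominator is psychotherapy starters; not enrolled if enrolment is taken over ne |
| One BA session, then no treatment | Dropout | Dropout |

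The definitions disagree in the second and third rows only.

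**Dropout, second row.** Let d be the true dropout from depression treatment, the same for movers and non-movers, and s the share of psychotherapy enrollees who move to antidepressants before a second session. The document gives neither. All movers are scored as dropouts, so scored dropout = s + (1 − s)d. With d = 20%:

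- s = 5%: 0.05 + 0.95 × 0.20 = 24%
- s = 10%: 0.10 + 0.90 × 0.20 = 28%
- s = 20%: 0.20 + 0.80 × 0.20 = 36%

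With no early movers in control, control stays at 20% and the artificial difference is 4, 8 or 16 percentage points. At s = 20% it would be 18 points if d = 10% (28% against 10%) and 14 points if d = 30% (44% against 30%).

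**Dependence on the control arm.** The artificial difference is (s in intervention − s in control) × (1 − d). With d = 20%:

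- 10% against 5%: 28% − 24% = 4 points
- 5% against 5%: 24% − 24% = 0
- 0% against 5%: 20% − 24% = −4 points

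**Enrolment, third row.** Let e be the share of eligible patients who enrol in any depression treatment and b the share of those enrollees who take antidepressants only. Psychotherapy enrolment over ne = e(1 − b). Assume e = 80% in both arms and b = 0 in control:

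- b = 10%: 0.80 × 0.90 = 72%
- b = 20%: 0.80 × 0.80 = 64%
- b = 30%: 0.80 × 0.70 = 56%

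Control would stay at 80%, although uptake of treatment is the same in both arms.

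**Mixed reading.** If the Table 1 denominator te were combined with the session rule, patients on antidepressants from the start would also be dropouts. Taking all patients on antidepressants with fewer than two sessions as 10%, 20% or 30% of te, the first formula gives 28%, 36% or 44% against 20%. No section states this combination.

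**After the fix.** With numerator and denominator both covering any treatment, and a move counted as continuing treatment, dropout is d in both arms. Under the same assumptions the artificial difference is zero.

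**The case against.** The strongest defence is that the outcomes text is coherent by itself. It limits its rates to psychotherapy and gives antidepressants their own rates, and Table 3 follows the same split. A patient who never started psychotherapy is then, on the ordinary reading, outside the psychotherapy dropout rate. A patient who left after one session did leave psychotherapy, so the label is right for a psychotherapy-specific rate. Patients stepped up after two or more sessions count as engaged, and the pathway also allows medication to be added while BA continues. Reach already provides a comparison that does not depend on type of treatment.

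Much of this stands. A reader might infer that all intervention patients on antidepressants will be counted as dropouts and that the comparison is therefore certainly biased. The document does not support that. For patients on antidepressants from the start it requires the mixed reading; for patients who switch, it applies only before the second session. Some control clinics may also offer antidepressants, so a control share of zero cannot be assumed.

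The conflict between the sections remains. Table 1 promises any-treatment rates, and separate psychotherapy and antidepressant rates do not supply them: neither shows whether a patient who left BA is still being treated. Reach measures participation, not dropout. Even on the coherent reading, an early mover is scored differently in the two places, and psychotherapy enrolment over all eligible patients would understate uptake in the intervention arm.

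**Conclusion.** The definitions conflict and need to be reconciled. Following the outcomes text, a move to antidepressants before the second BA session is scored as dropout although depression treatment continues. If psychotherapy enrolment is taken over ne, patients who choose antidepressants from the start count as not enrolled. Because antidepressants are built into the intervention arm and control care is described mainly as counselling, the comparison could disadvantage collaborative care.

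The size cannot be fixed from the document. The illustrative excess of 4 to 16 points in dropout rests on assumed early-move shares of 5% to 20%, 20% true dropout in both arms and none of these moves in control. It vanishes if the shares are equal and reverses if control has more. The larger range of 8 to 24 points that a reader might derive from the mixed reading should not be quoted as the plan's bias. An effect on completion cannot be sized, because the article gives no separate threshold for completion. Only secondary implementation outcomes are affected, and those derived from them; neither primary outcome is.

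**What to change.** Reconcile Table 1, Table 3 and the section on secondary implementation outcomes so that each rate has one numerator and one denominator.

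1. Use the any-depression-treatment rates of Table 1 for the comparison between arms. Count a recorded move from psychotherapy to antidepressants as continuing treatment, and score dropout only when no depression treatment of either kind continues.
2. Report the psychotherapy rates among those who started psychotherapy, in both arms, with moves to antidepressants as a separate category.
3. Keep the antidepressant prescription and adherence rates as planned.
4. Replace the BA labels in Table 3 with wording that fits control clinics, and carry the same definitions into sustainability and equity.

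This changes how outcomes are scored, not the care given. The cost is wording and a few extra tabulations. Tracking of contacts and care provided is described for intervention clinics. Control clinics' routine records would also have to show whether any depression treatment continues, and this should be confirmed; the Table 1 definition of dropout already requires it.
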